### Data management

The study will be regularly monitored by the Data Management and Monitoring Committee of the Good Clinical Practice Department of Beijing Hospital of Traditional Chinese Medicine, Capital Medical University. The Data Management and Monitoring Committee is independent of the trial researchers and has no competing interests. The Data Management and Monitoring Committee will monitor the overall quality and integrity of the data, examine the original case report forms, interview the researchers, verify the record of adverse events, and confirm that the study conforms to the principles of this protocol.

### Sample size calculation

In a previous study [20], the WOMAC score after treating by fire needle was 52.83 ± 20.85 and 59.92 ± 23.80 days in the filiform needle group. Based on the relevant literature [21] we have consulted, the minimal clinically important difference (MCID) of WOMAC scores was set at 6.7. It is set that the inspection level is 0.05 (*α* = 0.05, two-sided), and the power of the test is 0.2 (*β* = 0.2), using a 1:1 ratio, i.e., the sample size of fire needle group (*n*_1_) = the one of filiform needle group = 40. Considering the loss rate of 20% or less, a sample size of 50 per group and a total number of 100 participants will be recruited during the entire study accordingly.

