**Methods and analysis:**

This is a prospective randomized controlled superiority clinical trial to evaluate the efficacy and safety of fire needle acupuncture compared to filiform needle acupuncture for knee osteoarthritis. A total of 100 participants will be randomly assigned to two different groups. Participants will receive fire needle acupuncture treatment in the fire needle group, while participants in the filiform needle group will be treated with a filiform needle at the same acupuncture points as the fire needle group. All participants will receive 6 weeks of treatment (2 times per week). The primary outcome is the change of the Western Ontario and McMaster Universities Osteoarthritis Index, and the secondary outcomes include the change of the visual analog scale and 12-item Short Form Health Survey from baseline to endpoint.

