### Statistical analysis

Using the statistical software of SPSS 20.0, *p* < 0.05 for a two-sided test will be regarded as the standard to judge the significance of the difference. The measurement data will be expressed as mean ± standard deviation ($$ \overline{x} $$ ± *s*). If the precondition of a parametric test is satisfied, *t* test will be chosen. For non-parametric data, a Wilcoxon rank sum test will be used. The counting data will be expressed as frequency (or rate), which is calculated by a chi-square test or Fisher’s exact test.

The results of the study will be statistically analyzed according to the principle of intention-to-treat (ITT) and per-protocol population (PP). In ITT, all enrolled participants who have treated at least once will be analyzed. In PP, all participants who meet the study criteria, have completed the observation, have good compliance, do not use prohibited drugs during the study, and completed the study contents will be analyzed. Finally, comparison of the consistency of the results between ITT and PP will be conducted. The multiple imputation method will be used to process the missing data for the primary outcome.

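### The 40 per group (50 with loss) does not follow from the stated WOMAC inputs: on those inputs power is about 26–29%, not the 80% implied by β = 0.2

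*Protocol article*

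**What the plan says.** The Sample size calculation section of the protocol article gives the planning data as "the WOMAC score after treating by fire needle was 52.83 ± 20.85 and 59.92 ± 23.80 days in the filiform needle group". It adds that "the minimal clinically important difference (MCID) of WOMAC scores was set at 6.7", takes α = 0.05 two-sided and β = 0.2 (the wording gives the power itself as 0.2), and uses 1:1 allocation. It then states 40 per group. Allowing for loss of up to 20%, "a sample size of 50 per group and a total number of 100 participants will be recruited".

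Three other statements bear on the sum:

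- The Abstract and the Study design section both call the trial a superiority trial.
- The Abstract defines the endpoint on the change scale: "The primary outcome is the change of the Western Ontario and McMaster Universities Osteoarthritis Index".
- The Statistical analysis section plans a t test, or a rank sum test if the assumptions fail, with p < 0.05 "for a two-sided test will be regarded as the standard to judge the significance of the difference". It mentions no baseline adjustment.

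**The concern.** The planning difference is about a third of the planning SD: 6.7/22.37 = 0.30 and 7.09/22.37 = 0.32. A standardised difference of that size normally needs more than 150 per group for 80% power, so 40 looks about four times too small.

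This is the only justification given for the sample size, and it concerns the primary outcome. If it is wrong, a trial facing a true effect equal to its own MCID would more likely than not miss it, and the null result could be read as equal efficacy. On the quoted SD, results that did reach significance would overstate the effect. The Discussion presents the trial as groundwork for larger multicentre trials, and either error would carry forward into them.

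**Working it through.** **Inputs** (all from Sample size calculation): means 52.83 and 59.92, so the difference is 59.92 − 52.83 = 7.09; SDs 20.85 and 23.80; MCID 6.7; two-sided α = 0.05 (z = 1.960); β = 0.2 (z = 0.842); ratio 1:1.

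**Pooled SD** = √[(20.85² + 23.80²)/2] = √500.58 = 22.37.

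**Trying to reproduce 40 per group.** Using n = 2(1.960 + 0.842)² × SD²/d²:

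| Target difference d | n per group, normal approximation | n per group, t-based |
|---|---|---|
| 6.7 | 175.05, so 176 | 177 |
| 7.09 | 156.3, so 157 | 158 |

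Other superiority readings also fail:

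- Either arm's SD alone gives 153–199 (d = 6.7) or 136–177 (d = 7.09).
- One-sided α = 0.05 with the pooled SD gives 138 or 124.
- A power of 0.2 taken literally gives 28 or 25 with the pooled SD.

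The only combination found near 40 at the stated α and β adds the two differences: 7.09 + 6.7 = 13.79, which gives 41.3, so 42 (t-based 43). That is how a non-inferiority margin enters a formula. It may be where the figure came from, but this is a guess, and it would not fit a superiority trial tested for a difference.

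**Loss step.** 40/(1 − 0.20) = 50. This is correct.

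**Power of the stated design** (noncentral t, SD 22.37):

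| | d = 6.7 | d = 7.09 |
|---|---|---|
| 40 analysed per group | 26.3% | 28.8% |
| 50 analysed per group | 31.7% | 34.8% |

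With either arm's SD alone, power at 40 per group stays between 24% and 33%.

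**What the design can detect** (SD 22.37):

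| | 40 per group | 50 per group |
|---|---|---|
| Standard error = 22.37 × √(2/n) | 5.00 | 4.47 |
| Smallest significant observed difference = t × SE | 1.991 × 5.00 = 10.0 | 1.984 × 4.47 = 8.9 |
| True difference detected with 80% power | 14.2 | 12.7 |
| Average significant estimate if the truth is 6.7 (simulated) | about 13 | about 12 |

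**Could the change scale rescue it?** The quoted SDs are for scores after treatment. The documents give no SD of change and no correlation, so the correlation r is an assumption here. With equal SDs at both visits, SD of change = 22.37 × √[2(1 − r)]. Power for 6.7 is then:

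| r | SD of change | 40 per group | 50 per group |
|---|---|---|---|
| 0 | 31.6 | 16% | 18% |
| 0.5 | 22.4 | 26% | 32% |
| 0.7 | 17.3 | 40% | 48% |
| 0.8 | 14.2 | 55% | 65% |

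For 80% power at 6.7 with 40 per group, the analysed SD must be 10.6 or less, which needs r of about 0.89 (about 0.88 with baseline adjustment). With all 50 analysed, r must still be about 0.86.

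**The case against.** Nobody can defend 40 as the result of the printed inputs. The serious objections are to the power figures and to how far the conclusion is taken.

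- **The SD is on the wrong scale.** Power of 26–29% uses the SD of post-treatment scores, while change is analysed. For change scores these figures correspond to r = 0.5, and a higher correlation would raise them. This stands as a caveat: the figures describe the stated inputs, not the trial's true power, which is unknown. It does not rescue the sum, because 80% needs a correlation near 0.89 that the document neither states nor supports.
- **The analysed number may exceed 40.** Loss is put at 20% or less, and missing primary outcomes are to be imputed, so the effective number lies between 40 and 50. This is fair, but 50 per group reaches only 32–35% on the stated SD.
- **Overestimation among significant results depends on the SD.** This is correct. At r = 0.7 with 50 per group, the significance cut-off falls to 1.984 × 17.33 × √(2/50) = 6.9, close to the planning difference. The cut-offs of 10.0 and 8.9 hold only for SD 22.37.
- **The power of 0.2 is a slip.** β = 0.2 stands beside it, so 80% is clearly meant. It needs correcting but adds no weight to the main error.
- **Reporting rules belong in the SAP, which is not shown.** This is true, and the error in the sample size does not depend on them. A later SAP cannot make the printed sum correct.

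**Conclusion.** The stated sample size is wrong as written. On the protocol's own difference, SDs, α and β, 80% power needs 158–177 analysed per group, about four times the 40 stated. The design as stated has 26–29% power at 40 per group and 32–35% at 50. It reaches 80% only for differences of 14.2 or 12.7 points, against an MCID of 6.7.

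These figures assume a two-sided two-sample t test and an analysed SD of 22.37. The SD of change could move them either way. Power stays below 80% at 6.7 unless the baseline-to-week-6 correlation is about 0.89 with 40 per group, or about 0.86 with 50 (equal SDs assumed). Confidence that the calculation fails is high. This must be fixed, because it is the sole basis for the sample size.

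**What to change.** Keep the 100 participants and rewrite the Sample size calculation section:

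1. State power 0.8 with β = 0.2, and remove the unit of days from the WOMAC score.
2. Remove the implication that 40 per group gives 80% power.
3. If an SD of change or a baseline-adjusted SD was intended, state it with its source, name the target difference on that scale, and redo the sum.
4. If no such SD is available, say that 40 evaluable per group with a post-treatment SD of 22.4 gives about 26% power at 6.7 and 29% at 7.09, and 80% only for differences of about 14 points. Say also that the SD of change is unknown.
5. State, here or in the SAP, that the result will be given as a mean difference with a 95% confidence interval read against 6.7, and that non-significance will not be taken as equal efficacy.

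The cost is a rewritten paragraph and a less favourable power statement. No extra participants are needed. Keeping the 80% claim at the quoted SD would instead take 177/0.8 = 221.25, so 222 per group, for 6.7, or 158/0.8 = 197.5, so 198 per group, for 7.09.

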### Outcome measures

The efficacy of the treated patients will be evaluated before treatment and 6 weeks after intervention. The main efficacy indicator is the WOMAC questionnaire for knee pain, stiffness, and function. The secondary efficacy outcomes are VAS for generalized pain and SF-12 for quality of life. The collected information and data will be maintained confidentially.

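### The sample size uses SDs of post-treatment WOMAC scores while the abstract makes change in WOMAC primary, so the stated 80% power is not established for the primary comparison

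*Protocol article*

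**What the plan says.** Four places in the Protocol article bear on this point.

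- **Abstract, Methods and analysis:** "The primary outcome is the change of the Western Ontario and McMaster Universities Osteoarthritis Index", taken from baseline to endpoint. This is the only place that says which form of WOMAC is primary.
- **Outcome measures:** "The main efficacy indicator is the WOMAC questionnaire for knee pain, stiffness, and function". It adds that "The efficacy of the treated patients will be evaluated before treatment and 6 weeks after intervention". It does not say whether the final score or the change is compared.
- **Sample size calculation:** "the WOMAC score after treating by fire needle was 52.83 ± 20.85 and 59.92 ± 23.80 days in the filiform needle group" (the word days is a slip; these are WOMAC points). Then "the minimal clinically important difference (MCID) of WOMAC scores was set at 6.7". The significance level is 0.05, two-sided. The text prints "the power of the test is 0.2" next to β = 0.2, which I read as 80% power. The result is 40 per group, raised to 50 for losses of up to 20%.
- **Statistical analysis:** a t test or a Wilcoxon rank sum test, two-sided. It does not name the WOMAC variable to which the test applies and states no baseline adjustment.

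None of these sections gives an SD of change, a baseline SD or a correlation between baseline and final score.

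**The concern.** A power statement describes one test on one variable. Here the spread belongs to the score after treatment, while the variable declared primary is the change. The two SDs can differ widely in either direction, depending on how strongly baseline and final scores correlate. Without that correlation, nothing links the printed SDs to the primary comparison.

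What is at stake is how a non-significant result can be read. To say whether such a result speaks against a 6.7-point difference, the sponsor needs the power for the variable actually tested. Recomputing N from the same SDs would correct the arithmetic but leave this gap open.

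**Working it through.** **Inputs from the Sample size calculation section.** SDs 20.85 and 23.80; difference 6.7 (the MCID) or 59.92 − 52.83 = 7.09 (the observed difference); two-sided α 0.05; power 80%; 1:1 allocation.

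**Assumptions, because the article gives no figure.** Correlation r from 0.3 to 0.9, and equal SDs at baseline and at the end of treatment.

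**Step 1: the plan's own figure.** Pooled SD = √[(20.85² + 23.80²)/2] = √[(434.72 + 566.44)/2] = 22.37. With n = 2(1.960 + 0.842)² × SD²/difference²:

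- 6.7 points: 7858/44.89 = 175.05, so 176 per group (177 by the exact t-test calculation).
- 7.09 points: 7858/50.27 = 156.3, so 157 per group (158 by the exact calculation).

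The stated 40 is not reproduced. With 40 per group, the t test on final scores has 26% power for 6.7 points and 29% for 7.09. The last step, 40/(1 − 0.20) = 50, is correct.

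**Step 2: from final score to change.** With equal SDs, SD(change) = SD × √[2(1 − r)]. This equals the final-score SD at r = 0.5, exceeds it below 0.5 and is smaller above. Under randomisation the expected between-group difference is the same for final score and change, so only the SD is in question.

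**Step 3: consequences for 6.7 points** (two-sample t test, noncentral t).

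| r | SD of change | n per group for 80% | Power for change, 177 per group | Power for change, 40 per group |
|---|---|---|---|---|
| 0.3 | 26.47 | 247 | 66% | 20% |
| 0.5 | 22.37 | 177 | 80% | 26% |
| 0.7 | 17.33 | 106 | 95% | 40% |
| 0.8 | 14.15 | 71 | 99% | 55% |
| 0.9 | 10.01 | 36 | above 99% | 84% |

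The fourth column isolates the mismatch: it takes an N that is right for final scores and asks what it delivers for change. For 7.09 points, 158 per group gives the same 66%, 80%, 95% and 99% at r = 0.3, 0.5, 0.7 and 0.8. The last column also carries the arithmetic fault of step 1.

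**Step 4: when 40 per group would be enough.** For 80% power the SD of change must be about 10.56 (6.7 points) or 11.18 (7.09 points). Then r = 1 − (10.56/22.37)²/2 = 0.89, or 1 − (11.18/22.37)²/2 = 0.88.

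**Step 5: if the SDs differ.** If the baseline SD is k times the final SD, SD(change) = SD × √(1 + k² − 2rk). The break-even correlation is then k/2, for example 0.4 at k = 0.8 and 0.6 at k = 1.2.

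**The case against.** The strongest reply has three parts.

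**The primary variable may not be change at all.** The word appears in the abstract's definition only. The Outcome measures and Statistical analysis sections leave it open, and the sample size section points to the final score. Abstract wording can be loose. This stands as far as it goes, but it does not remove the problem: the one explicit definition and the planning figures still disagree, and the article does not settle which governs.

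**Post-treatment SDs are a common stand-in, and the direction of error is unknown.** This is correct. A reader might infer that even a correctly computed N would fall short of 80% for change. The article does not support that. With equal SDs, such an N falls short only below r = 0.5 and meets or exceeds 80% from there upward, and no r is given.

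**The low power at 40 per group is mostly a different fault.** This also stands. Power is already only 26% to 29% on final scores, with no mismatch at all. For 6.7 points, moving to change at r = 0.7 or 0.8 raises it from 26% to 40% or 55%. A reader might blame the whole shortfall on the choice of variable; the figures do not allow that.

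What remains is that correcting the arithmetic alone would give 158 to 177 per group, a figure that could still be wrong for change in either direction: for 6.7 points the need is 247 at r = 0.3 and 71 at r = 0.8.

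**Conclusion.** The point holds in a limited form. The planning SDs are those of the final score, the only explicit definition makes change primary, and nothing in the article connects the two. The stated 80% power is therefore unverified for the primary comparison. The mismatch by itself is not shown to cause a shortfall.

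For the mismatch alone, a correctly computed N has between about 66% and 99% power for change over r = 0.3 to 0.8. For the 40 per group actually stated, power for 6.7 points is 20% to 55% over the same range, and 80% would need an r close to 0.9.

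These figures rest on equal SDs at both times, on assumed values of r, on an unadjusted t test, and on reading the printed power of 0.2 as β. Severity is moderate: a stated figure on which the trial relies needs correcting, but conduct of the trial is not affected.

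**What to change.** Use one WOMAC variable in the abstract and in the Outcome measures, Sample size calculation and Statistical analysis sections. There are two ways to do this.

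1. **Change is primary.** Name it in the Outcome measures and Statistical analysis sections. In the sample size section, replace the post-treatment SDs with the SD of WOMAC change, from the cited study if it reports one. Otherwise use SD × √[2(1 − r)] with the assumed r stated. Then restate the power of 40 analysable per group over a range of r, for example 0.3 to 0.8 (20% to 55% for 6.7 points).
2. **The final score is primary.** Say so in the abstract and in the Outcome measures and Statistical analysis sections, and restate the power of 40 analysable per group on that basis: about 26% for 6.7 points and 29% for 7.09.

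The choice should be made without sight of outcome data by group, and the printed power of 0.2 corrected in the same edit.

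The cost is a reworded paragraph and a few aligned phrases. No extra patients or new data are needed. The downside is a less favourable stated power, which would also limit what may be concluded from a non-significant result.

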### Statistical analysis

Using the statistical software of SPSS 20.0, *p* < 0.05 for a two-sided test will be regarded as the standard to judge the significance of the difference. The measurement data will be expressed as mean ± standard deviation ($$ \overline{x} $$ ± *s*). If the precondition of a parametric test is satisfied, *t* test will be chosen. For non-parametric data, a Wilcoxon rank sum test will be used. The counting data will be expressed as frequency (or rate), which is calculated by a chi-square test or Fisher’s exact test.

The results of the study will be statistically analyzed according to the principle of intention-to-treat (ITT) and per-protocol population (PP). In ITT, all enrolled participants who have treated at least once will be analyzed. In PP, all participants who meet the study criteria, have completed the observation, have good compliance, do not use prohibited drugs during the study, and completed the study contents will be analyzed. Finally, comparison of the consistency of the results between ITT and PP will be conducted. The multiple imputation method will be used to process the missing data for the primary outcome.

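### The primary WOMAC comparison is an unadjusted two-sample test although baseline WOMAC is measured; adjusting for it would cut the variance by 15% to 25% at plausible correlations

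*Protocol article*

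**What the plan says.** The Statistical analysis section of the protocol article covers all continuous data with one rule: "If the precondition of a parametric test is satisfied, *t* test will be chosen". If the assumptions fail, a Wilcoxon rank-sum test replaces it. Neither test takes a covariate, and no baseline adjustment is mentioned anywhere in the article.

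Under Outcome measures, efficacy (WOMAC as main indicator, VAS and SF-12 as secondary) is assessed before treatment and at 6 weeks, so each participant should have a baseline value. The abstract defines the endpoint as a change: "The primary outcome is the change of the Western Ontario and McMaster Universities Osteoarthritis Index". The Statistical analysis section does not say whether the test is applied to changes or to week-6 scores. The Sample size calculation uses post-treatment scores, not changes: "the WOMAC score after treating by fire needle was 52.83 ± 20.85 and 59.92 ± 23.80 days in the filiform needle group".

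**The concern.** Baseline WOMAC is likely to predict week-6 WOMAC. A two-sample test either ignores that information (final scores) or uses it with a fixed coefficient of 1 (change scores). ANCOVA estimates the coefficient from the data.

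Two consequences follow:

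- **Precision.** The standard error is larger than it need be. That matters more in a trial that is short of information on its own figures.
- **Chance imbalance.** In any one randomisation the arms will differ somewhat at baseline. A final-score comparison leaves this uncorrected and a change-score comparison over-corrects it. The described block randomisation mentions no stratification by baseline severity that would limit it.

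The article names the test itself. This is therefore a choice it has made, not a detail left to an analysis plan.

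**Working it through.** **Inputs from the Sample size calculation section**

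- Two-sided test: "the inspection level is 0.05 (*α* = 0.05, two-sided"). β = 0.2, so the intended power is 0.80, although the text calls 0.2 the power.
- Target difference: "the minimal clinically important difference (MCID) of WOMAC scores was set at 6.7".
- Post-treatment SDs of 20.85 and 23.80. Pooled SD = √((20.85² + 23.80²)/2) = 22.37.
- Evaluable n: "the one of filiform needle group = 40", "using a 1:1 ratio". Allowing for 20% loss, 40/(1 − 0.2) = 50 per arm.

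**Assumed, because the article does not give them:** the baseline to week-6 correlation r, and a baseline SD equal to the post-treatment SD.

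**Step 1: the plan's own figure.** With the normal approximation, n per arm = 2 × (1.960 + 0.842)² × 22.37² / 6.7² ≈ 175.05, so 176. With the earlier study's observed difference of 7.09 it is 157. The stated 40 is not reproduced; it would need an SD of about 10.7. A final-score t test for 6.7 points has 26% power with 40 per arm and 32% with 50 (noncentral t). The description of the trial as underpowered therefore rests on its own inputs.

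**Step 2: relative variance of the three estimators** (final-score t test = 1)

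- Final-score t test: 1
- Change-score t test: 2(1 − r)
- ANCOVA: 1 − r²

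ANCOVA/change = (1 − r²)/(2(1 − r)) = (1 + r)/2, which is below 1 for every r below 1. ANCOVA/final = 1 − r², which is below 1 unless r = 0. The change-score test is worse even than the final-score test when r is below 0.5.

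**Step 3: variance and power** (difference 6.7, SD 22.37, two-sided 0.05, noncentral t)

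| r | ANCOVA variance vs change | ANCOVA variance vs final | Power, 50 per arm: change → ANCOVA | Power, 40 per arm: change → ANCOVA |
|---|---|---|---|---|
| 0.3 | 35% lower | 9% lower | 24% → 34% | 20% → 28% |
| 0.5 | 25% lower | 25% lower | 32% → 40% | 26% → 33% |
| 0.6 | 20% lower | 36% lower | 38% → 46% | 32% → 38% |
| 0.7 | 15% lower | 49% lower | 48% → 55% | 40% → 46% |
| 0.8 | 10% lower | 64% lower | 65% → 70% | 55% → 60% |

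At r = 0.5 the gain equals enlarging each arm from 50 to 50/0.75 ≈ 67.

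**Step 4: chance baseline imbalance.** The SE of the baseline difference is 22.37 × √(2/50) = 4.5 points with 50 per arm and 22.37 × √(2/40) = 5.0 with 40. The first is 4.5/6.7 = 67% of the target difference. For a baseline difference D, the final-score estimate is shifted by r × D and the change-score estimate by −(1 − r) × D. At r = 0.5, with D of one SE and 50 per arm, the shift is about 0.5 × 4.5 = 2.2 points either way, a third of 6.7. At r = 0.7 it is 3.1 points for final scores and 1.3 for change scores.

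**Step 5: what ANCOVA does not do.** For 80% power (normal approximation) it needs 132 per arm at r = 0.5 and 90 at r = 0.7. It reaches 80% with 40 per arm only if r is about 0.88.

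**The case against.** The strongest reply is that nothing here is invalid. Under 1:1 randomisation a t test on change is unbiased on average and keeps its type I error. That is correct, and the point is one of efficiency. It still stands, because the article fixes the less efficient test when the covariate is already collected.

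Further objections carry some weight:

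- **The abstract points to change scores**, so baseline already enters by subtraction and the final-score column is the less likely reading. This is fair, and the 15% to 25% reduction is the figure to use. Subtraction does not remove the loss, since (1 + r)/2 is below 1 for any r below 1.
- **r and the baseline SD are unknown.** True. The size of the gain depends on both, but its direction does not depend on r within the range shown.
- **Forty evaluable per arm is the planned information, not 50.** Also fair. At 40 the gain is about 6 to 7 percentage points for r of 0.5 to 0.7.
- **Precision and imbalance are not separate harms.** Over repeated randomisations, imbalance is part of the unadjusted variance and is already in the standard error. They should not be added together. Imbalance matters for interpreting the one randomisation that occurs.
- **The low power is a sample-size defect.** It is, and it is the larger problem. Adjustment recovers only part of the shortfall.

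**Conclusion.** The concern holds. The article commits to an unadjusted two-sample comparison of an outcome measured at baseline, and ANCOVA is more precise on either reading of that comparison. Against change scores, variance falls by 25% to 15% for r from 0.5 to 0.7. With 50 per arm this adds about 6 to 9 percentage points of power. It also removes a dependence on baseline imbalance whose typical size, at r = 0.5, is about 2.2 points.

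These sizes assume an unreported r, equal SDs of 22.4 at both visits and a true difference of 6.7. The conclusion does not extend to bias or type I error, and ANCOVA leaves the trial well short of 80% power unless r is close to 0.88. The change should be made, but it does not decide whether the trial is valid.

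**What to change.** Make the primary analysis a linear model of week-6 WOMAC total on treatment arm and baseline WOMAC total. Report the adjusted mean difference with its 95% CI and interpret it against 6.7. This is consistent with an endpoint defined as change: with baseline in the model, the treatment estimate is the same whether the dependent variable is the week-6 score or the change. Use the same model, each outcome with its own baseline, for VAS and SF-12. Keep the unadjusted t test and the rank-sum test as supportive analyses only.

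The planned multiple imputation for the primary outcome can stay, provided the imputation model contains at least arm and baseline WOMAC.

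The cost is a sentence or two in the Statistical analysis section, with no new data and a model that SPSS provides. Because recruitment was due to start in November 2020, the change should be a dated amendment made before anyone sees outcome data by arm; adjustment chosen later would look data-driven. The sample size needs its own correction.

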#### WOMAC (Western Ontario and McMaster Universities Osteoarthritis Index)

WOMAC is a standardized questionnaire used to evaluate the condition of subjects with osteoarthritis of the knee and hip, which assesses the three dimensions of pain, stiffness, and functional limitation [18] with 24 questions. The score range for each question is 0 to 4. The total score of WOMAC is on a scale of 0 to 96, and higher scores indicate more severe symptoms.

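### An unnamed check on the trial's own data decides whether the primary WOMAC comparison is a t test or a rank-sum test, so the quantity tested is not fixed in advance

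*Protocol article*

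**What the plan says.** The abstract of the protocol article defines the primary endpoint: "The primary outcome is the change of the Western Ontario and McMaster Universities Osteoarthritis Index". The section on WOMAC gives its range: "The total score of WOMAC is on a scale of 0 to 96".

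The Statistical analysis section has no separate paragraph for this endpoint. It covers all measured data with one rule. The summary is fixed: "The measurement data will be expressed as mean ± standard deviation". The test is conditional: "If the precondition of a parametric test is satisfied", the t test is chosen; "For non-parametric data, a Wilcoxon rank sum test will be used". No check, significance level or variable to be checked is given.

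The same section adds: "The multiple imputation method will be used to process the missing data for the primary outcome". It does not say what is pooled or how.

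The Sample size calculation section plans in WOMAC points: "the minimal clinically important difference (MCID) of WOMAC scores was set at 6.7". The 6.7 appears only there; no section says that the result will be judged against it.

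**The concern.** The two branches answer different questions. The t test asks whether mean WOMAC change differs between the arms. The rank-sum test asks whether values in one arm tend to be larger than in the other. If the arms respond with different shapes, one can be significant without the other. With no stated criterion, the choice for the confirmatory comparison is made once the data are in hand.

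Two practical gaps follow. A rank-sum p-value carries no difference in WOMAC points, the unit in which the trial is planned. And Rubin's rules combine an estimate and its standard error over imputed data sets, whereas the plan attaches neither to the rank-sum branch. The check could also pass in some imputed data sets and fail in others, and the rule does not say what happens then. The sample size allows for up to 20% loss, so imputation is likely to be needed.

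**Working it through.** **Inputs from the Sample size calculation section.** "the WOMAC score after treating by fire needle was 52.83 ± 20.85 and 59.92 ± 23.80 days in the filiform needle group" (the word for days is evidently a slip; these are WOMAC points). Difference: 59.92 − 52.83 = 7.09. Arm sizes: 40 analysed, and 40/(1 − 0.20) = 50 recruited, as stated. Whether 40 is right for these inputs is a separate question and does not affect this point.

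**Assumptions, because the document does not give them.** The check is Shapiro-Wilk in each arm at 0.05, with or without a Levene test at 0.05. No baseline WOMAC is given, so change scores use assumed baselines with mean 60-70, SD 18-22 and baseline-to-week-6 correlation 0.3-0.7.

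**Step 1: how often the rule switches.**
- Exactly normal data, by arithmetic: two checks at 0.05 give 1 − 0.95² = 9.75%; three give about 1 − 0.95³ = 14.3% if treated as independent. Simulation gives 9.7% and 14.7%.
- Post-treatment scores drawn as beta variables on 0-96. With m = mean/96, v = (SD/96)² and k = m(1 − m)/v − 1, the parameters are mk and (1 − m)k. Fire needle: m = 0.550, v = 0.0472, k = 4.25, giving (2.34, 1.91). Filiform: m = 0.624, v = 0.0615, k = 2.82, giving (1.76, 1.06).
- The primary endpoint is change, so the change-score row below is the relevant one.

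| Data | Share sent to rank-sum |
|---|---|
| Normal | about 10-15% |
| Change in WOMAC (assumed baselines) | about 10-20% (single runs 8-21%) |
| Post-treatment WOMAC, beta shape | 60-78% |
| Post-treatment WOMAC, normal cut off at 0 and 96 (mean 56, SD 22.4) | 9.6% |

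The last two rows show that the post-treatment figure depends on the assumed shape.

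**Step 2: does the choice change the verdict?** With the previous study's means and SDs (difference 7.09), the t test and the rank-sum test fall on opposite sides of 0.05 in 4.7% (40 per arm) and 5.2% (50 per arm) of trials with beta scores, in 5.8% and 6.9% with normal data, and in about 7% with change scores.

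**Step 3: type I error of the two-stage rule.**

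| Null | Two-stage rule | t test alone |
|---|---|---|
| Same shape in both arms (normal, gamma, lognormal, cut-off normal) | 4.7-5.2% | 4.7-5.1% |
| Same shape, change scores | 4.6-5.7% | 4.6-5.3% |
| Equal mean and SD, one arm gamma (shape 1.5-4), other normal | 6.6-9.2% | 4.7-5.9% |

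**Step 4: can the rank-sum branch be pooled?** Yes, once an estimate is named. The Mann-Whitney probability θ = U/(n₁n₂) has null variance (n₁ + n₂ + 1)/(12n₁n₂). At 50 per arm this is 101/30,000 = 0.00337, a standard error of 0.058. Rubin's total variance over m = 20 imputations is T = W + (1 + 1/20)B, with W the mean within-imputation and B the between-imputation variance. In 2,000 simulated null trials with 20% missing at random, the pooled test rejected in 4.6%. The plan names no such estimate.

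**Step 5: what fixing one test costs in sample size.** Very little either way: with normal data a rank-sum test throughout would need 40 × π/3 = 41.9, about 42 per arm, in place of 40.

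**The case against.** A t test, or a rank-sum test if assumptions fail, is a conventional summary rule in an article, and a full protocol or SAP that is not shown may name the check and the pooling method. Those who analyse the data are to be blinded to allocation, which limits selective choice. This stands as far as it goes. But the article states a data-dependent rule rather than leaving the matter open, and an SAP that only supplied the missing criterion would still leave two possible quantities for one primary endpoint.

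Four stronger readings are tempting, and the documents do not support them:

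- *The rank-sum branch cannot be pooled, so the imputed analysis cannot be run.* It can, for example through the Mann-Whitney probability (step 4). What is missing is the named estimate.
- *The rank-sum branch breaks a rule on the 6.7-point difference.* No such rule exists; 6.7 serves the sample size only. Arm means and SDs are to be reported whichever test is used, and a Hodges-Lehmann shift would be in WOMAC points under a location-shift assumption. The plan does not provide for that estimate.
- *Most trials would switch.* That comes from beta-shaped post-treatment scores, not from change.
- *The rule inflates type I error in general.* It does not when both arms share a shape. The 6-9% arises in a constructed case that nothing in the document suggests is likely.

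**Conclusion.** The concern holds as one of prespecification and estimand. The quantity tested for the primary endpoint depends on an unnamed check of the trial's own data, and the rank-sum branch gives no effect in WOMAC points and names nothing to pool. The practical size is modest: about 10-20% of trials would switch on change scores, and in about 5-7% the two tests disagree about significance at the planned difference. There is no general type I error problem. Where shapes differ at equal means and SDs, the 6-9% rejection rate means that a significant result need not reflect a difference in mean change.

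All rates rest on the assumed check, the assumed baselines and the assumed distributional shapes. That the quantity is left open needs none of these assumptions; it follows from the text. The check also buys little: at 40-50 per arm with equal allocation, the t test alone stayed between 4.5% and 5.9% in every null examined.

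**What to change.** In the Statistical analysis section, take the primary endpoint out of the general rule and give it one analysis. For example:

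> The primary analysis of WOMAC is the between-group difference in mean change from baseline to week 6 with its 95% confidence interval, estimated by a linear (t-type) model irrespective of any normality check and pooled over the multiple imputations by Rubin's rules. A Wilcoxon rank-sum test is a sensitivity analysis.

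Robust standard errors can be added if wanted. If the rank-sum sensitivity analysis is also to use the imputed data, name the estimate to be pooled; otherwise state that it uses observed data.

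The cost is a sentence or two of text, with no new data. The downside is slightly less power than the rank-sum test if the data turn out very skewed.
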